### Study population

This study started in the first quarter of 2021 and is currently under way in college students in Colorado, USA, including University of Colorado (Denver, Boulder, Colorado Springs, Aurora), Colorado State University (Fort Collins), Regis University (Denver), as well as Colorado Mesa University (Grand Junction). We envisage enrolment to be completed by April 2022 but would potentially continue beyond this if high SARS-CoV-2 transmission is documented. Students as well as faculty (and their family) are eligible to be enrolled.

### The FMS method

The FMS method has been successfully used to detect *Mycobacterium* in breath samples and recently adapted for COVID-19 testing.^12^ The sensitivity compared with regular nasal swab sampling has not been conclusively determined (which is part of this research project). The (preliminary) analytical sensitivity of this method was estimated around ≥10^4^ virus particles, which corresponds to a cycle threshold (Ct) value of 18–20 in the PCR and is in agreement with recent publications and sample testing by other colleagues at the University of Alberta, Canada.^13^

### Face mask selection

Commercial three-layer spunbond polypropylene masks will be provided to the participants, tested for breathability (95% filtration;KN95). Masks were approved by the occupational safety and health administration (OSHA) / food and drug administration (FDA). Each mask will be uniquely coded for tracking.

### Participant and public involvement

Participants were involved in the selection of best fitting masks in a pilot phase. Feedback was elicited regarding the acceptability and fit of different mask designs.

### PVA test strips

PVA test strips are provided by University of Leicester under a material transfer agreement and strips will be adhered to predetermined positions inside the face masks. PVA has a very good safety profile, being already used in cosmetic products (face masque) and is approved as hypoallergenic and non-toxic for humans.^14^ PVA has been used in diagnostic tests^15–17^ as well as medical device implant for orthopaedic surgery^18^ and for theranostic nanoplatform therapeutic imagery.^19^

### Sample size

This is an exploratory study. We aim for an up to 3300 individuals, including participants with confirmed SARS-CoV2 infection (index cases) and their contacts. These estimates are based on the conservative estimate of 5% transmission from index cases to a close contact. With a maximum of 300 index cases and ~10 contacts per index case, we estimate that we would detect ~150 secondary cases in contacts.

### Schedule of wearing masks

Participants will be asked to wear a mask with two PVA test strips adhered to the inside surface for 2 hours per day. Index cases will complete 7 days of mask wearing and if they test positive by the end of the 7-day period, they will be asked to continue for another 7 days up to day 14. Contacts will complete 7 days of mask wearing as long as they test negative. If testing positive in the first 7 days, they will complete an additional 7 days of mask wearing starting with the day when they first test positive. If by the end of this period they still test positive, the duration will be extended by 2-day intervals with their permission until two consecutive masks wear dates test negative (figure 2). On completion of 2 hours of wear by the participant, the face masks will be placed in a sealed plastic bag, collected daily and brought into the laboratory where the PVA strips will be put into tubes with viral transport medium (VTM). The VTM tubes with the PVA strips will be eluted and tested by PCR.

**Figure 2 F2:**
[figure not shown]
Polyvinyl alcohol (PVA) mask strip study, sampling plan for index case and contact.

### Self-administered nasal swabs

We ask the participants to collect a self-administered nasal swab daily by placing a nasal swab approximately 0.5 inches into one nostril and swabbing the inside of the nose. The swab is then immediately placed into a 15 mL conical tube containing 2 mL of VTM. Samples are put into a separate sealed bag and stored at 4°C until testing.

### Questionnaires

An electronic questionnaire is administered at the beginning of the mask-wearing period to collect basic demographics (age, gender) and to assess COVID-19 symptoms and activities (including the day when symptoms started). During the follow-up period, daily questionnaires are administered, and we have built in warning signs for potential severe COVID-19 that trigger an auto-alert, in which case we will proactively contact the participant and (a) ask the participant to stop wearing the masks and (b) advise the participant to seek medical care immediately. We also included an optional assessment of activities such as singing or exercising for index cases only (confirmed SARS-CoV-2 positive individuals) on 1 day using a separate second mask. In the future, the assessment of vital signs or specific symptoms could be added via wearable technologies or app-based recording (see, eg, https://www.hyfeapp.com/).

### Blood sampling

We will ask the participants to conduct self-sampling of blood using dried blood spots from finger pricks^20^ every third day (optional—filter papers and self-sealing bags provided along with the daily masks). Antibodies will be eluted from the filter paper to be used for serological investigations. These samples are going to be stored in separate sealed bags and picked up together with the other materials. After recovery, for example, between day 14 and 56 after quarantine/self-isolation, the participants are invited to return to the clinic for a venous blood sample (EDTA [Ethylenediaminetetraacetic acid] 20–30 mL). The blood is collected to investigate humoral, and T-cell based immune responses including cytokine profiles and other T-cell phenotypic surface markers that may be associated with transmissibility and clinical phenotype (eg, protection vs long COVID-19).

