Box 1ObjectivesStudy Identifier: clinicaltrial.gov identifier NCT05145803Objective 1: Identification of risk factors for, and rate of, infection in index cases and for transmission from index case to contacts.Objective 1.1: Describe demographics and evaluate risk factors for infection in index cases.Objective 1.2: Evaluate risk factors for transmission from index case to contacts (and their contacts), including viral load, clinical symptoms, vaccination status, activity and environmental metrics and immune response profiles (eg, neutralising antibodies, cytokine profiles—using a blood sample taken after recovery).Objective 1.3: Analyse the difference in the clinical status (symptomatic vs asymptomatic) for index cases as well as secondary cases by humoral and T-cell immune response profile (using the blood samples collected).Objective 1.4: Determine rate of and time to transmission, stratified by a variety of risk factors (including presence of clinical symptoms, activity and environmental metrics both in index cases and secondary contacts), analysing presymptomatic and asymptomatic exhalation of SARS-CoV-2 in contacts of index cases.Objective 2: In confirmed index cases and their contacts, quantify and determine the efficacy of the polyvinyl alcohol (PVA) test strip method for SARS-CoV-2 detection, comparing with the respective ‘reference standard’ (eg, nasal swab) collection method and correlating with the presence of antibodies.Objective 2.1: Assess the association between molecular detection by PVA test strip and molecular or antigen detection/quantification by initial reference diagnostic collection method.Objective 2.2: Assess the association between molecular detection by PVA test strip and molecular or antigen detection method (self-sampling) over the sampling/mask-wearing period.Objective 3: Due to the concern around emerging variants with higher transmissibility, carry out deep sequencing of PCR-positive samples (swabs as well as strips from masks) to derive the genotype of infecting virus.Objective 3.1: Share in timely fashion the results of the sequencing with the national/regional surveillance system.Objective 3.2: Assess the genetic similarities and differences of the SARS-CoV-2 variants by sequence comparison and by virological culture to assess cell-based infectivity of the strains.Objective 3.3: Determine the chain of transmission and relationship to clinical phenotype in the index case and contacts where viral RNA or culture permit.Objective 3.4: Analyse the difference in rate of transmission (see also objective 1) comparing different SARS-CoV-2 variants.

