### Data analysis

For objective 1, we will first conduct a descriptive analysis of the index cases. Then we will conduct a risk factor analysis using multivariable multilevel regression models to determine symptoms and behaviours that are associated with greater exhalation of SARS-CoV-2 virus, as detected by PVA test strips. We will also analyse presence and timing of symptoms in contacts to determine if PVA strips can detect SARS-CoV-2 in exhaled breath of presymptomatic and asymptomatic individuals. We will map the transmission dynamics visually, determine the length of exhalation of SARS-CoV-2 in cases and calculate the difference in rate of transmission by vaccination status. Using the convalescent blood sample, we will analyse different immune response profiles (neutralising antibodies, T-cell-based assays) stratified by clinical phenotype (symptomatic/asymptomatic, potentially using a symptom score for increased granularity).

To address objective 2, we will calculate the sensitivity and specificity of the FMS method, using the initial reference diagnostic method of the site in index cases. We will then calculate the sensitivity and specificity of the PVA test strips using the concurrently collected nasal swab as the reference standard for both index cases and their contacts. We will also correlate strip test positivity with Ct value of the PCR test (or viral load in a subset) over time and with presence of antibodies (IgA and IgG) over time.

To address the concern about emergence of new virus variants, in objective 3, the FMS eluted materials, original specimen and/or recovered live virus isolates will be subjected to deep sequencing to monitor genetic variants in the study population. We will use these data, when available, to calculate the infectiousness of each viral variant and to map the transmission chains and association with disease in contacts. We will provide the sequence information of identified SARS-CoV-2 variants (and aliquot of material) to national and global data warehouses for public health surveillance of virus variation that may impact disease transmission and resistance to vaccines. The remaining materials will be stored for longer term so that they can be accessed for public health surveillance purposes.

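### Convalescent blood is drawn in a wide, illustrative window counted from quarantine/self-isolation, and the planned phenotype comparison of immune profiles does not account for time of draw

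*Protocol article*

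**What the plan says.** The Blood sampling section of the protocol article describes one venous sample, taken once the participant has recovered, and offers its timing only as an example: "between day 14 and 56 after quarantine/self-isolation, the participants are invited to return to the clinic for a venous blood sample". Its purpose is also given there: "The blood is collected to investigate humoral, and T-cell based immune responses including cytokine profiles", together with other T-cell markers that may relate to transmissibility and clinical phenotype.

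The sample serves objective 1.3 in Box 1: "Analyse the difference in the clinical status (symptomatic vs asymptomatic) for index cases as well as secondary cases by humoral and T-cell immune response profile".

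For this objective the Data analysis section says "we will analyse different immune response profiles (neutralising antibodies, T-cell-based assays) stratified by clinical phenotype", possibly with a symptom score for finer grading. The last paragraph of that section says the laboratory analyses will depend on the experiments and on the number of confirmed cases. It names ANOVA and Student's t-test as likely, leaves room for other analyses, and allows parametric or non-parametric methods according to distribution. Neither paragraph mentions the interval between infection, or first positive test, and the blood draw.

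**The concern.** Humoral and cellular immune measures are expected to change over the weeks after an infection, so a single sample is interpretable only together with its timing. Two features of the plan leave that timing loose.

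- **The clock.** Quarantine applies to exposed contacts and self-isolation to cases, and they begin from different events. One day count is attached to both. For a contact who turns positive, the text does not say which of the two starts the count.
- **The analysis.** Stratifying by phenotype, or comparing two groups with a t-test or ANOVA, takes no account of when each person was drawn.

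At stake is the answer to objective 1.3. Uncontrolled timing adds variance to every immune measure. If timing also happens to be associated with symptom status, part of a timing difference would be reported as an immune difference between phenotypes.

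**Working it through.** The documents give no figure for timing effects, so there is none to reproduce on this point. The sample size fixes how many cases could contribute: 300 index cases × 10 contacts × 5% = 150 secondary cases, which matches the article. At most 300 + 150 = 450 cases could enter objective 1.3, fewer if some decline the visit.

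**Inputs from the article**
- Window: day 14 to day 56 (Blood sampling).
- Contacts may first test positive at any point in their first 7 days of mask wearing, and their mask schedule then restarts from that day (Schedule of wearing masks). The blood draw is given no such restart.
- Dates available: a positive test for every index case (Box 2, inclusion criteria); daily self-swabs, "We ask the participants to collect a self-administered nasal swab daily"; and the day of symptom onset from the questionnaire, which exists for symptomatic people only.

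**Inputs not in the article (assumptions)**
- Time from infection to end of isolation: 5 to 20 days.
- Difference in mean timing between phenotypes, d: 0 to 10 days.
- Antibody half-life, h: 30 to 90 days, with simple log-linear decline.

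**Step 1: spread from the window.** Width = 56 − 14 = 42 days. With uniform draws, SD = 42/√12 = 12.1 days.

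**Step 2: time since infection.** With a 5-day lag, draws fall on days 14 + 5 = 19 to 56 + 5 = 61. With a 20-day lag, they fall on days 34 to 76.

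**Step 3: noise.** On the log2 scale the timing SD is 12.12/h, which is 0.135 at h = 90 and 0.404 at h = 30. As fold changes these are 2^0.135 = 1.10 and 2^0.404 = 1.32.

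**Step 4: possible confounding.** Overlap of the two windows = 1 − d/42. Standardised shift = d/12.12. Spurious ratio = 2^(d/h).

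| d (days) | Overlap | Shift (SD) | Ratio, h = 90 | Ratio, h = 30 |
|---|---|---|---|---|
| 0 | 100% | 0 | 1.00 | 1.00 |
| 2 | 95% | 0.16 | 1.02 | 1.05 |
| 5 | 88% | 0.41 | 1.04 | 1.12 |
| 10 | 76% | 0.82 | 1.08 | 1.26 |

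The row d = 0 is fully compatible with the document.

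**Step 5: what each remedy reaches.** Counting from the first positive test removes the variation due to isolation length and to the mixed clock. It leaves the 42-day spread if the width is kept. A covariate for days from first positive test to draw deals with that spread. Neither reaches the lag from infection to first positive test.

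**The case against.** The strongest reply is that nothing here is shown to bias the comparison. A reader might infer that symptomatic and asymptomatic cases are sampled at systematically different times since infection. That would require isolation length, or the lag from infection to diagnosis, to depend on symptom status. The article gives no isolation length, no rule linking it to symptoms, and no lag. The Data management section mentions institutional protocols on informing cases, contact tracing and quarantine, but not how long isolation lasts. This part of the objection stands in full.

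Two passages might seem to supply the link. The draw comes after recovery, which is a clearer event for someone with symptoms; and the Introduction says asymptomatic people are less likely to be tested. They make an association plausible but establish neither its existence nor its direction.

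Further points also stand:
- The window is illustrative, and counting from the end of isolation is a natural reading but not stated text.
- The quarantine/self-isolation distinction separates contacts from index cases. If objective 1.3 is analysed within each of those groups, that distinction does not bias it.
- Two people with the same response drawn at opposite ends of the window would differ 2^(42/90) = 1.38- to 2^(42/30) = 2.64-fold under the assumed half-lives. That reflects window width and would arise under any anchor, so it does not measure harm from this one.

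Finally, the study is exploratory, the list of methods is open-ended, and covariate detail may sit in an analysis plan not shown. That limits the weight of the point but does not remove it. The sampling clock is a design element stated in the article, and the methods it names for the comparison leave timing out.

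**Conclusion.** The point holds in a limited form. Time since infection is controlled neither by the stated sampling window nor by the stated analysis of objective 1.3. The certain consequence is added variance: a draw-time SD of about 12 days if draws are uniform, or 1.10- to 1.32-fold noise under the assumed half-lives. Confounding by timing is possible, with a spurious ratio between 1.00 and 1.26 for assumed shifts of 0 to 10 days, but the document does not demonstrate it. The half-lives, the log-linear decline, the uniform draws and the shifts are all assumptions. The change is worth making because it is nearly free and uses dates the study captures or must already know. The point does not invalidate the objective.

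**What to change.** **Analysis (Data analysis section, objective 1).** Compare symptomatic with asymptomatic cases by a regression of each immune measure on phenotype. Include days from first positive PCR or antigen test to blood draw, index or secondary status, and vaccination status as covariates. This can also be applied to samples already drawn.

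**Sampling (Blood sampling section).** For research draws still to be scheduled, count the window from the first positive test for every case, still after recovery. Do not offer symptom onset as an alternative starting point: asymptomatic cases have none, so the clock itself would then depend on the phenotype being compared.

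**Cost.** A change of wording, a few degrees of freedom and slightly more analysis work, with no extra visit or sample. The lag from infection to first positive test remains uncontrolled, may itself differ by symptom status, and should be reported as a limitation.

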### Laboratory methods

In a biosafety cabinet, PVA strips are removed from inside of the face masks, by cutting them at the ends where they are adhered using double-sided tape. Each strip is placed into a 15 mL conical tube containing 2 mL of viral transport medium (VTM) and incubated at room temperature for at least 30 min to allow PVA to dissolve. Samples are stored at 4°C until testing. After collection and elution of the strip, testing will be carried out with the following tests in order to validate the results from the FMS against the reference test:

First line: PCR from the eluate of the strip.Second line: antigen test, which gives a positive/negative/indeterminate response.Third line: virus culture to determine if virus is infectious.

In brief, for PCR testing, two approaches are used. In the first approach, samples (PVA strips and nasal swabs) are briefly vortexed to thoroughly mix. Viral RNA is extracted from 200 µL of sample using the Mag-Bind Viral DNA/RNA 96 Kit following the manufacturer’s protocol. Quantitative real-time PCR is performed using CDC 2019-nCoV primer probes and EXPRESS qPCR Supermix and SuperScript. Samples are considered positive if their N1 Ct is less than 38. In the second approach, samples (PVA strips and nasal swabs) are briefly vortexed to thoroughly mix. Viral RNA is extracted from 45 µL of sample by digesting with 5 µL of Proteinase K (PK, NEB) for 15 min at 60°C. PK is inactivated for 5 min at 95°C. Reverse transcription droplet digital PCR (RT-ddPCR) was performed on PK digested sample using CDC 2019-nCoV primer probes and One-Step RT-ddPCR Advanced Kit for Probes (Bio Rad). Samples are considered positive if their N1 concentration is >0.25 copies/µL. The RNA extracted from the FMS and potentially recovered live viruses will be used as basis for deep sequencing.^3^

One of our aims is to validate a novel antigen assay for testing PVA strips from the masks. For this assay, electrodes were prepared according to Samper *et al*.^21^ For sample analysis, 20 µL of PVA mask sample or virus standard was added to the functionalised electrode and incubated for 40 min, and then rinsed with PBST (phosphate buffer saline with tween) and PBS(phosphate buffer saline) using solid stream spray bottles. Virus standards were inactivated with 0.1% Igepal and diluted in Hanks’ Balanced Buffer Solution with 0.1% Tween80 and 0.1% Igepal. Following sample incubation, 20 µL of a 0.5 µg/mL horseradish peroxidase-antibody solution was added and incubated for 25 min, and then rinsed with PBST and PBS using solid stream spray bottles. For measurement, 50 µL of 3,3′,5,5′-tetramethylbenzidine was added to the electrode and incubated for 2 min. After 2 min, chronoamperometry was run at 0.0 V for 2 min.

### Contactless delivery and pick-up of supplies

All masks and other samples are delivered/picked up at the residence of the participants and placed in their own sealed bag with a unique identifier. All exposed masks and collected sample kits are individually packaged compliant with UN3314 packaging safety requirements. For the decontamination of surfaces and personal protective equipment, we will use 70% alcohol for immediate decontamination of exposed surfaces, especially those that the participant may have touched. For longer-term decontamination, we will use 10 µM methylene blue spray that allows for up to 10 hours of decontamination in light.^22^ Hand hygiene solutions will be used to clean hands at the end of each drop-off/pick up activity.

### Data management

All study data will be collected using Research Electronic Data Capture (REDCap). Data cleaning and quality control assessments will be conducted on the REDCap survey data, and a weekly data dashboard will be produced to support the study team in detecting issues with data collection. Indicators of severe disease will be monitored daily. Test results from the reference test, the additional molecular tests, antibody tests and the PVA strip test will be linked to survey data using a unique anonymized study identification number, and data will be stored on a secure internal server with restricted access at the University of Colorado with no personal identifiers. The study analyst will hold the key to the personal identifiers and will unblind results as necessary to inform the institution of any previously unknown positive cases, so that they can follow the institution’s protocols regarding informing the case, contact tracing and quarantine. All data will be cleaned, merged and analysed using SAS V.9.4 (Cary, North Carolina, USA), to ensure replicability of the process and analysis.

### Data analysis

For objective 1, we will first conduct a descriptive analysis of the index cases. Then we will conduct a risk factor analysis using multivariable multilevel regression models to determine symptoms and behaviours that are associated with greater exhalation of SARS-CoV-2 virus, as detected by PVA test strips. We will also analyse presence and timing of symptoms in contacts to determine if PVA strips can detect SARS-CoV-2 in exhaled breath of presymptomatic and asymptomatic individuals. We will map the transmission dynamics visually, determine the length of exhalation of SARS-CoV-2 in cases and calculate the difference in rate of transmission by vaccination status. Using the convalescent blood sample, we will analyse different immune response profiles (neutralising antibodies, T-cell-based assays) stratified by clinical phenotype (symptomatic/asymptomatic, potentially using a symptom score for increased granularity).

To address objective 2, we will calculate the sensitivity and specificity of the FMS method, using the initial reference diagnostic method of the site in index cases. We will then calculate the sensitivity and specificity of the PVA test strips using the concurrently collected nasal swab as the reference standard for both index cases and their contacts. We will also correlate strip test positivity with Ct value of the PCR test (or viral load in a subset) over time and with presence of antibodies (IgA and IgG) over time.

To address the concern about emergence of new virus variants, in objective 3, the FMS eluted materials, original specimen and/or recovered live virus isolates will be subjected to deep sequencing to monitor genetic variants in the study population. We will use these data, when available, to calculate the infectiousness of each viral variant and to map the transmission chains and association with disease in contacts. We will provide the sequence information of identified SARS-CoV-2 variants (and aliquot of material) to national and global data warehouses for public health surveillance of virus variation that may impact disease transmission and resistance to vaccines. The remaining materials will be stored for longer term so that they can be accessed for public health surveillance purposes.

In addition, the samples and data generated in this study will provide ample opportunity for laboratory analysis such as immune profiling or viral genome copy quantification and sequencing. Specific analyses will depend on the experiments and number of confirmed cases, however, will likely include ANOVA (analysis of variance), student t-test and other analyses. Laboratory data will be examined for normality of distribution as necessary, and the appropriate parametric or non-parametric descriptive analyses will be conducted to determine significant differences.

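### The comparison of immune profiles by symptom status names no handling of vaccination, so a phenotype difference could partly reflect vaccine coverage

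*Protocol article*

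**What the plan says.** Objective 1.3 (Box 1) is to "Analyse the difference in the clinical status (symptomatic vs asymptomatic) for index cases as well as secondary cases by humoral and T-cell immune response profile". The Data analysis section carries this out on the convalescent sample: "we will analyse different immune response profiles (neutralising antibodies, T-cell-based assays) stratified by clinical phenotype". The bracket that follows elaborates only the phenotype ("symptomatic/asymptomatic, potentially using a symptom score for increased granularity").

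Vaccination status appears in three other places:
- The Introduction expects breakthrough infections and asks for vaccine details to be monitored.
- Objective 1.2 lists risk factors for transmission "including viral load, clinical symptoms, vaccination status, activity and environmental metrics and immune response profiles".
- The sentence just before the immune-profile sentence in Data analysis plans to "calculate the difference in rate of transmission by vaccination status".

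Multivariable multilevel models are named in the same paragraph, but for viral exhalation on the strips. For laboratory work, including immune profiling, the closing paragraph of Data analysis says the analyses "will likely include ANOVA (analysis of variance), student t-test and other analyses" and that significant differences will be sought.

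**The concern.** Symptomatic and asymptomatic cases need not have the same vaccine coverage. If coverage differs between them and vaccinated people have higher neutralising titres, the groups will differ in titre even when phenotype has no relation to immunity within vaccinated or within unvaccinated people. The article recognises vaccination as relevant to transmission and lists it beside immune profiles, yet does not connect it to this comparison. A reader of the results could then not tell an immune profile that goes with asymptomatic infection from a difference in vaccine coverage. The argument is clearest for neutralising antibodies. T-cell and cytokine profiles may be affected to a different degree.

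**Working it through.** **The plan's own figures.** The only figures are in Sample size: 300 + 300 × 10 = 3300 individuals, and 300 × 10 × 0.05 = 150 secondary cases. Both reproduce. Neither belongs to the immune-profile comparison, for which no figure is given. They bound the number of infected people giving blood at 300 + 150 = 450, if everyone accepts the invitation.

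**Model.** Assume no phenotype effect within vaccination strata. Let v be the share of cases vaccinated, a1 and a0 the asymptomatic share among vaccinated and unvaccinated cases, and d the vaccine effect on the marker in within-stratum SDs. All four are assumptions. Then:
- asymptomatic share overall: A = v·a1 + (1 − v)·a0
- vaccinated share among asymptomatic cases: pA = v·a1 / A
- vaccinated share among symptomatic cases: pS = v·(1 − a1) / (1 − A)
- spurious difference: d·(pA − pS)
- variance in each group: 1 + d²·p·(1 − p)
- rejection rate: two-sided 5% normal approximation with unequal variances

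**One case in full.** Take v = 0.5, a1 = 0.5, a0 = 0.2, d = 1 and N = 450.
- A = 0.25 + 0.10 = 0.35, giving groups of 157.5 and 292.5.
- pA = 0.25/0.35 = 0.714 and pS = 0.25/0.65 = 0.385, so the difference is 0.330 SD.
- The variances are 1 + 0.714 × 0.286 = 1.204 and 1 + 0.385 × 0.615 = 1.237.
- SE = √(1.204/157.5 + 1.237/292.5) = 0.109, and the difference is about 3.03 SEs, so the test rejects in 85.7% of studies.

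**Range at v = 0.5.**

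| a1 / a0 | d | pA / pS | Spurious difference (SD) | Rejects, N = 100 | Rejects, N = 450 |
|---|---|---|---|---|---|
| 30% / 30% | 0.5 or 1.0 | 0.500 / 0.500 | 0 | 5.0% | 5.0% |
| 40% / 30% | 0.5 | 0.571 / 0.462 | 0.055 | 5.7% | 8.4% |
| 40% / 30% | 1.0 | 0.571 / 0.462 | 0.110 | 7.6% | 16.9% |
| 50% / 20% | 0.5 | 0.714 / 0.385 | 0.165 | 11.9% | 36.9% |
| 50% / 20% | 1.0 | 0.714 / 0.385 | 0.330 | 29.7% | 85.7% |

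Higher coverage shrinks the effect. At v = 0.8 the last row becomes 0.195 SD, with 14.8% and 48.6%.

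**The same on a titre scale.** Assume a residual SD of 1.5 log2 units and equal groups of 75 or 150.
- Vaccinated 70% vs 50% (asymptomatic vs symptomatic), vaccine effect 2 log2: difference 0.2 × 2 = 0.4 log2, a ratio of 2^0.4 = 1.32, with rejection in 28% (75 per group) and 49% (150 per group).
- Vaccinated 80% vs 40%, same effect: 0.8 log2, a ratio of 1.74, with 80% and 98%.
- Vaccinated 60% vs 50%, effect 1 log2: 0.1 log2, with 7% and 9%.

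**After adjustment.** Comparing within vaccination strata, or adjusting for vaccination, returns the bias to 0 and the rejection rate to 5% under this model.

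**The case against.** The best defence is that nothing here is fixed. A reader might infer that the plan commits to an unadjusted t-test or ANOVA. It does not: the tests are described as likely, other analyses are left open, and the choice depends on the experiments and case numbers. ANOVA can itself carry vaccination as a factor, and naming phenotype as the stratifier does not exclude others. A full protocol or analysis plan, not shown, may adjust. This stands, and it lowers the weight of the point. What remains is that the article names vaccination for the neighbouring analysis and only phenotype for this one.

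A reader might also infer that the day of blood draw biases the contrast. The window "between day 14 and 56 after quarantine/self-isolation" is introduced only as an example. Timing would bias the comparison only if it differed between phenotypes, which nothing in the documents suggests, and the calculation has no timing term. That reading is not supported.

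Nor do the documents state that vaccination changes symptom status or antibody level; this is a condition of the argument. If either link is absent, there is no bias.

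Finally, Objective 1.3 may simply ask which profile accompanies asymptomatic infection, whatever its source. On that reading vaccine-induced immunity is part of the answer and the crude comparison is legitimate. That is a good reason to keep the crude description, but it does not make that description sufficient for attributing a difference to phenotype.

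**Conclusion.** The point holds as a minor improvement. Phenotype is the only stratifier named for the convalescent immune profiles, in a study that expects mixed vaccination histories. If vaccination is related to both symptom status and neutralising antibody level, the contrast is confounded. The size cannot be derived from the documents. Across the assumptions tried it ranges from no bias, with a 5% rejection rate, to a titre ratio of 1.74 with 98% rejection at 150 per group. That upper end needs a large coverage gap and equal groups that the article does not promise, since the venous sample is by invitation. The calculation covers a single antibody-type marker only. The study is declared exploratory and this is one of its sub-objectives, so the consequence is an ambiguous finding, with no threat to the main conclusions.

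**What to change.** Add to the Objective 1.3 analysis that, besides the crude description by phenotype, immune profiles will be compared within vaccination strata. Alternatively, use a linear model of log titre on phenotype, adjusted for vaccination status at infection (doses and interval where available) and for days from first positive test to blood draw. The draw-day term takes up variation in sampling time and does not presume a bias. Flag anyone vaccinated between infection and draw.

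Vaccination status is already a planned variable. The article does not say that the draw date is recorded, so this should be confirmed. The cost is analysis wording, a few more model terms and slightly wider intervals.
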